**Conclusions::**

ICG lymphangiography allows a surgeon to see locoregional lymphatics of a tumor site in real time and tailor colon and mesentery resection margins to meet oncological and functional needs. More data is needed to make this approach more widespread.

## Introduction

### Background and rational

Navigational surgery including mapping and tailoring of resection margins can be a solution to the major problem of colon cancer surgery: finding “the least possible not to compromise oncological safety” resection clearance for each patient. Mentioned concept has already been discussed^[1,2]^. But although the idea that all patients are different and therefore require different approaches sounds reasonable, this notion has not met sufficient response because yet there is no tool with proven effectiveness to implement it.

However, there is a lot of evidence on ICG fluorescent imaging for visualization of locoregional lymphatic paths of colonic lesions^[2,3]^, which can guide tailoring. ICG was firstly implemented as a sentinel lymph node detection (SLND) tool but was found to lack accuracy and standardization. Ankersmit *et al* analyzed 8 studies describing 227 SLN procedures in a meta-analysis in 2019 and observed low pooled sensitivity of 63%, negative predictive value 81% and detection rate of 94%^[4]^. The same year Villegas-Tovar *et al* reported similar findings in another meta-analysis of ICG SLND accuracy for colon cancer: they calculated detection rate of 91% (80–98%), sensitivity of 64.3% (51–76%), and specificity of 65% (36–85%) – and concluded that overall ICG performance for detection of lymph node metastases is poor^[5]^. So, it was shown that ICG does help to visualize lymphatics, but it does not work for SLND in colon cancer.

Moreover, assessment of fluorescence and fluorescent lymph node harvest are affected by multiple factors. In particular, 2023 systematic review and meta-analysis of 58 prospective designed studies by Lucas *et al* showed that injection time had a significant impact on aberrant drainage detection favoring preoperative tracer injection^[6]^. The same year Kinoshita *et al* in their series of 56 cases observed both cases with metastatic lymph nodes only in the area along the ICG-stained vascular pedicles and lymph node metastasis in areas along the ICG-unstained vascular pedicles^[7]^.

This situation can be explained by the fact that presence of fluorescence is affected by tumor factors. Kakizoe *et al* compared distribution of cancer sites in lymphatic nodes according to hematoxylin and eosin staining to fluorescent picture: lymph nodes occupied by cancer cells up to 90–100% showed no fluorescence, and in nodes with smaller proportion of occupation fluorescence was missing in cancer sites^[8]^. The same pattern was observed by Ushijima *et al*, who also reported negative correlation between such factors as tumor’s depth of invasion and presence of fluorescence, and pN+ and presence of fluorescence respectively^[9]^. So, in cases of colon cancer focusing on fluorescence of specific lymphatic nodes, or seeking for sentinel nodes with ICG lymphangiography does not seem to be a reliable approach.

On the contrary, ICG imaging of the whole locoregional lymphatic collector is beneficial. Repeatedly reported data on surgical results after ICG mapping suggest that lymph node mapping without focusing on specific nodes might be useful for identifying resections’ extent during operations for colon cancer. In a series of 18 patients, Cahill *et al* observed 22% of fluorescing lymphatic nodes outside the initial resection plan^[10]^. Nishigori *et al* reported ICG lymph node mapping led to 23.5% change in the extent of lymphadenectomy, and 16.7% change in the colon resection plan^[11]^. Moreover, Watanabe *et al* reported that in cases of central vascular ligation, the use of ICG helped to identify appropriate central vessels to be dissected, as well as to determine the appropriate separation line of mesentery so that the whole observed lymph flow is included into specimen^[12,13]^. And Daibo *et al* showed that indocyanine green fluorescence imaging-guided laparoscopic right-sided colectomy could increase the number of total, intermediate, and central lymph nodes retrieved^[14]^. Thus, it seems that multiple groups of patients are likely to benefit from ICG lymphatic mapping, because this technique provides a possibility to tailor resection margins so that they fulfill oncological demand of regional lymphatic flow removal. Trial registration information is presented in Table 1.

**Table 1 T1:** Trial registration

Primary registry and trial identifying number	ClinicalTrials.gov NCT05468827
Date of registration in primary registry	21.07.2022
Source of material support	FSBI "NMRC of Oncology named after N.N. Petrov" of the MoH of the Russian Federation
Primary sponsor	FSBI "NMRC of Oncology named after N.N. Petrov" of the MoH of the Russian Federation
Contact for public queries	[name] [contact]
Contact for scientific queries	[name] [contact]
Title	ICG Fluorescence Guided Lymph Node Mapping for Determination of Bowel Resection Margins in Colon Cancer (ISCAPE)
Countries of recruitment	Russian Federation
Problem studied	Surgical treatment for colon cancer
Intervention	Lymphatic mapping by ICG
Key eligibility criteria	Adult female or male, 18 years or older, with signed informed consent, and diagnosed primary colon cancer.
	Inclusion Criteria: pathologically confirmed adenocarcinoma of the colon, T1-4aN0-2bM0-1b, clinical indications to colonic resection, ECOG – 0–2.
	Exclusion Criteria: acute bowel obstruction, bleeding or perforation, adjacent organ invasion or peritoneal carcinomatosis, contraindications to ICG administration.
Study type	Interventional with single group assignment
	Allocation: N/A
	Primary purpose: diagnostic
	Phase II
Date of first enrolment	26 July 2022
Target sample size	101 patients
Recruitment status	Recruiting
Primary endpoint	Proportion of pN+ patients with affected lymph nodes detected only within margins of ICG distribution
Secondary endpoints	Incidence of adverse events related to ICG lymphatic mapping, feasibility of ICG lymphatic mapping for colon cancer, incidence of lymph node metastases outside conventional resection margins (10 cm), colon cancer lymphatic spread patterns, proportion of operations which extent is affected by ICG lymphatic mapping
Protocol version	v. 3.1

### Objectives and study hypothesis

In this trial it is investigated whether the zone of lymphatics’ fluorescence visualized after subserosal ICG injection reflects the region of metastatic spread from a colon segment affected by a tumor. Even though it is assumed that ICG fills in the whole regional lymphatic collector (with all affected nodes), hypothetically, ICG mapping procedure might lead to one of six scenarios (Fig. 1): ICG spreads within conventional resection margins (affected lymph nodes within/outside fluorescence zone), or ICG spreads beyond conventional resection margins (affected lymph nodes within fluorescence zone and within/beyond conventional resection margins), or ICG spreads beyond conventional resection margins (affected lymph nodes outside fluorescence zone and within/beyond conventional resection margins). So, these groups’ detection and analysis will help to make important assumptions and considerations regarding role of ICG lymphatic mapping in colon cancer surgery. For instance, if no affected lymph nodes are observed beyond margins of ICG spread in subcategory of patients with fluorescent zone smaller than conventional resection margins, it will mean that extent of colon and mesentery resection plan can be decreased to fit ICG spread. And on the contrary, if frequency of lymph node metastases beyond ICG spread margins makes method’s sensitivity suboptimal, efficacy of ICG lymphatic mapping will have to be reconsidered.

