#### Endpoints

Primary endpoint
Proportion of pN+ patients in which affected lymph nodes are detected only within margins of ICG distribution (number of patients with affected lymph nodes located within ICG distribution margins divided by the number of all patients with pN+).

Secondary endpoints
Incidence of adverse events related to ICG lymphatic mapping (time frame: 30 days after operation);feasibility of ICG lymphatic mapping for colon cancer (proportion of cases with ICG spillage affecting interpretation);incidence of lymph node metastases outside conventional resection margins – 10 cm (proportion of patients with aberrant lymphatics leading to affected lymph nodes);colon cancer lymphatic spread pattern (descriptive data on incidence of D1, D2 and D3 lymphatic collector metastases and frequencies of D1 collector metastases depending on distance from primary tumor);proportion of operations which extent is effected by ICG lymphatic mapping (number of patients with change of operation plan due to mapping results divided by the number of patients).

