#### Patient enrollment

Patients are enrolled by investigating physician. The study in general and the intervention itself together with information about indocyanine green and associated risk are discussed with the patient, and time and opportunity are provided to allow the patient to familiarize with the informed consent. Should any questions arise, they are answered by investigating physician, and enough time for decision making is provided to the patient. After informed consent is signed, patient is considered as enrolled into the trial.

Patients with signed informed consent, meeting all inclusion criteria and having no exclusion criteria are assigned to elective colonic resection with intraoperative ICG lymphatic mapping. Surgeon in charge decides on extent of colonic resection and planned approach.

Data regarding patients’ demographics, tumor’s TNM, size, and location as well as planned surgery are recorded in case report form.

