#### Postoperative care

Postoperative care is provided according to local guidelines. Adverse events are registered according to Clavien–Dindo classification. Treatment for complications follows local standards. Data on beginning, duration and treatment for complications is documented in patients’ case report form. Time frame for recording of adverse events is 30 days after surgery. No follow-up is done after this point.

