### Sample size calculation and statistical analysis

As the study is aimed to access if ICG mapping can be used to reliably define resection margins in colon cancer surgery, a case of affected lymph nodes only within fluorescence margins was regarded as a true positive case, no fluorescence in pN0 – true negative, pN+ because of metastatic lymph nodes outside fluorescence zone – false negative, pN0 despite presence of fluorescence – false positive.

Sample size of 101 patients was calculated using Buderer method^[19]^ with a confidence level (1 – *α*) of 0.95 as a minimum of cases required to test accuracy of lCG lymphatic mapping for estimated sensitivity of 0.99 and precision (margin of error) of 0.03. This resulted in sensitivity threshold of 0.96. The calculation was performed for minimum acceptable kappa (k0) of 0.6, expected kappa (k1) 0.9. The resultant estimated power (1 – *β*) is 0.96. The average of pN+ cases in our center (42%) was used as prevalence – proportion of outcome (p).

For statistical analysis of primary endpoint, sensitivity will be calculated according to standard formula (number of true positive cases divided by sum of true positive and false negative cases) and its meaning will be compared to the estimated 0.99 ± 0.03. For analytical purposes other measures of accuracy will be calculated as well.

“Intent-to-treat” analysis will be performed, thus once enrolled patients are to be analyzed, irrespective of received treatment. To focus on specificities ICG spread regardless of influence of patients with treatment deviations and those with unsuccessful ICG injection, “per-protocol” analysis will be performed as well.

For secondary endpoints type of analysis will depend on nature of the data. Descriptive statistics will be used to depict feasibility of ICG lymphatic mapping, incidence of adverse events, incidence of lymph node metastases outside conventional resection margins and proportion of operations which extent is affected by ICG lymphatic mapping. Lymph node metastases pattern will be assessed as calculation of frequency of affected nodes related to number of studied nodes in each group. Parametric and non-parametric criteria will be used to compare mean values and contingency tables.

In cases of missing data, should more than 10% of data be missing, the variable will be deleted, because estimates are likely to be biased^[20]^. In other situations multiple imputations will be used.

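### Zero positive nodes beyond the dye in an unsized subgroup cannot show that resection may be reduced, and the primary sensitivity includes patients in whom a miss could not be seen

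*Protocol article*

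**What the plan says.** **The inference.** Under Objectives and study hypothesis, the protocol article describes six possible relations between dye spread, conventional margins and affected nodes. It then takes one case: "if no affected lymph nodes are observed beyond margins of ICG spread in subcategory of patients with fluorescent zone smaller than conventional resection margins". From that outcome it concludes, without qualification, that the bowel and mesenteric resection plan may be reduced to match the dye.

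**The sample size.** The section on sample size and statistical analysis gives one calculation only: "Sample size of 101 patients was calculated using Buderer method", for an "estimated sensitivity of 0.99 and precision (margin of error) of 0.03". It adds: "This resulted in sensitivity threshold of 0.96". No size, expected share or confidence bound is given for the small-zone subgroup.

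**What pathology can see.** The same section defines a false negative as a pN+ patient with metastatic nodes outside the fluorescent zone. The primary endpoint divides by all pN+ patients. Trial design, the Figure 3 legend and Pathology report show that nodes are located and examined in the removed specimen.

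**What sets the specimen.** Under Patient enrollment: "Surgeon in charge decides on extent of colonic resection and planned approach". Surgical procedure has the influence of dye spread on margins recorded, and one secondary endpoint is the "number of patients with change of operation plan due to mapping results divided by the number of patients". Postoperative care limits adverse-event recording to 30 days and adds: "No follow-up is done after this point".

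**The concern.** There are two separate problems.

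1. **Zero events is weak evidence in a small group.** The subgroup is an unknown part of about 42 pN+ patients. A count of zero there is compatible with a miss rate well above what the trial itself would accept. Yet the conclusion drawn from it, that less tissue can be removed, is the one with the largest safety consequence in the article.

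2. **A false negative needs harvested tissue beyond the dye.** Two kinds of patient escape the count:
   - A pN+ patient whose specimen nowhere extends past the dye border can only be a true positive.
   - A patient whose only positive nodes lay beyond the zone and were left in place is classed pN0 and leaves the denominator.

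   Both push the primary sensitivity upward. The effect should be concentrated where mapping changed the extent or where the dye reached beyond conventional margins. For the same reason, the incidence of metastases outside 10 cm counts only those in tissue that was removed.

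**Working it through.** **Inputs from the protocol article:** sensitivity 0.99, precision 0.03, confidence 0.95, success threshold 0.96, and "The average of pN+ cases in our center (42%) was used as prevalence".
**Assumed, because the article gives no figure:** the number n of pN+ patients in the small-zone subgroup, the share u of pN+ patients with no tissue beyond the dye border, and a true sensitivity of 0.90 as a test case.

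**Step 1. Reproduce the plan's figure.**
- pN+ needed = 1.96² × 0.99 × 0.01 / 0.03² = 42.26
- Total = 42.26 / 0.42 = 100.6, rounded up to 101. The stated figure is reproduced.
- Expected pN+ = 0.42 × 101, about 42.

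This sizes overall sensitivity only.

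**Step 2. What zero events shows.** The exact two-sided 95% upper limit is 1 − 0.025^(1/n). The chance of zero events at a true 10% miss rate is 0.9^n.

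| pN+ in subgroup (n) | Upper limit | Chance of zero events |
|---|---|---|
| 10 | 30.8% | 0.349 |
| 20 | 16.8% | 0.122 |
| 30 | 11.6% | 0.042 |
| 42 (all pN+) | 8.4% | 0.012 |

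The threshold of 0.96 implies a tolerated miss rate of 1 − 0.96 = 4%. Every limit in the table exceeds it. One-sided 95% limits, 1 − 0.05^(1/n), do not rescue the inference: 25.9% at n = 10 and 6.9% at n = 42.

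For zero events to exclude a miss rate above 4%, the subgroup would need ln(0.025)/ln(0.96), rounded up to 91 pN+ patients. The one-sided figure is 74. Even if every patient belonged to the subgroup, that means 91/0.42 = 217 patients in total (one-sided 74/0.42 = 177), against 101 planned.

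**Step 3. Direction and possible size of the verification bias.** If a share u of pN+ patients cannot be false negatives, observed sensitivity = 1 − (1 − Se)(1 − u). With 42 pN+ patients the 96% rule needs at least 41 successes, since 41/42 = 0.976 and 40/42 = 0.952.

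| u (assumed) | Observed sensitivity when the true value is 0.90 | Chance of at least 41/42 |
|---|---|---|
| 0% | 0.900 | 0.07 |
| 25% | 0.925 | 0.17 |
| 50% | 0.950 | 0.37 |

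This is an illustration only. It treats the share u as wholly uninformative and leaves out the patients reclassified as pN0.

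**The case against.** **The subgroup sentence is only an example.** It is introduced as an instance. The formal rule is overall sensitivity of 96% or higher, and the Abstract says more data are needed. An exact limit for an exploratory subgroup is also ordinary content for an analysis plan that is not shown. This lowers the weight of the sentence but does not repair it: the inference is printed here in conclusive terms, and no analysis plan can make zero events in this subgroup support it.

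**The verification gap barely touches the quoted subgroup.** This largely stands. Where the zone is smaller than conventional margins and the specimen is taken to those margins, tissue beyond the dye is present and misses can be seen up to the specimen edge. A reader might infer that a false negative is impossible in that subgroup. The article does not support this, because nowhere does it say that surgeons trim to the dye border. The gap bears mainly on the primary endpoint and on zones reaching past conventional margins.

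**The bias can be sized from the Introduction.** A reader might take the plan-change rates cited there (16.7% for colon resection, 23.5% for lymphadenectomy) as the share of uninformative patients. They are not. They come from an outside series and measure altered plans, not specimens ending at the dye border. A resection extended on one side can still include tissue beyond the zone elsewhere.

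**Appendix S1 is not shown.** It describes the mapping procedure and may contain a rule on tissue beyond the border. If so, the second problem shrinks, and the first is unaffected.

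**Much of the data is already collected.** True: borders are marked and photographed, and each node is located relative to them. What the text shown lacks is an analysis that uses this.

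**Conclusion.** The concern holds in two parts of unequal certainty.

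The zero-event inference is unsupported at any subgroup size this trial can reach. The upper limit is 8.4% in the best case and 31% with 10 pN+ patients, against an implied tolerance of 4%. With a true 10% miss rate, zero events in 10 patients would occur 35% of the time. Only the sizes of 10, 20 and 30 are assumptions; the best case uses the protocol's own 42%.

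The upward bias in the primary sensitivity follows from the definitions in the text shown, but its size is unknown because the share of affected patients is not given. The rise from 7% to 17% or 37% in the chance of passing shows what shares of 25% or 50% would do and is not an estimate. The trial's sensitivity result is not thereby shown to be wrong, and no position is taken on the right extent of resection.

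**What to change.** 1. **Reword the subgroup inference.** Replace the conclusion with a commitment to report the number of pN+ patients in the small-zone subgroup, the number with metastases beyond the zone, and the exact upper confidence limit. Call the result hypothesis-generating for a confirmatory trial.
2. **Derive one variable.** From the marked and photographed specimens, record for each pN+ patient whether tissue beyond the dye border was harvested.
3. **Keep the primary endpoint as defined and add a sensitivity analysis** restricted to pN+ patients with such tissue. Base any statement about extent on those patients, noting that nodes past the specimen edge remain unseen.
4. **Keep all patients in the denominator of the 10 cm endpoint** and label the result a lower bound. Restricting it to specimens longer than 10 cm could select patients whose resection was extended because of dye or suspected disease.

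The cost is one variable from material already recorded, one extra analysis and revised wording. The restricted analysis will have a smaller denominator and a wider interval.

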**Figure 1. F1:**
[figure not shown]
Possible relations between ICG lymphatic spread, conventional resection margins and lymphatic node metastatic involvement.

### Aims of the study

#### Primary aim of the study

To determine if ICG lymphatic mapping sensitivity is sufficient to guide resection margins selection in colon cancer surgery.

#### Secondary aims of the study

To determine safety and feasibility of ICG lymphatic mapping, incidence of lymph node metastases outside conventional resection margins (10 cm), colon cancer lymphatic spread patterns and proportion of operations which extent is affected by ICG lymphatic mapping.

### Trial design

#### Design

This is an interventional phase II trial with single group assignment investigating feasibility of defining colon resection margins for colon cancer with ICG by comparing lymphatic distribution of subserosally injected dye with actual spread of lymphatic metastases reported by pathologists after specimen examination.

This is a single center trial. To ensure adherence to the protocol and to avoid logistical and monitoring issues stemming from multicenter design, all patients are enrolled in one center. The study includes ICG lymphatic mapping procedure and extensive pathological evaluation of the specimen, which are not routinely performed in majority of centers. Also, the calculated sample size of 101 is a number of patients, which is possible to enroll in a single center during reasonable time period. So, the risks of type II error, methodological error leading to bias and contradicting results issue, resulting from single center approach were acknowledged and study protocol created to possibly minimize them and ensure that the statistical hypothesis is tested.

Since the main focus of the study is investigation of ICG lymphatic mapping feasibility and currently there is no gold standard of lymphatic mapping for colon, no control group was included.

After signing an informed consent and undergoing screening procedure eligible patients are assigned for colonic resection with ICG lymphatic mapping. The fluorescence is assessed before specimen removal (Fig. 2) and its mesenteric distribution is marked by surgeon on the specimen (Fig. 3). During pathological examination each lymph node is assessed both for presence of metastases and for its exact location in relation to margins of ICG distribution (each lymphatic node is classified according to Japanese classification of lymphatic node groups^[15]^; D1 nodes are also classified according to their distance from primary tumor^[16]^). All screening, intraoperative, postoperative, and pathological data is recorded for further analysis. Protocol synopsis is presented in Table 2.

